**Methods/design:**

This is a single-blind, multicentre, randomized controlled trial. At least ninety-three community-dwelling older adults with MCI aged 60 or above will be recruited. They will be randomly allocated into four groups: Physical Training alone (PT), Cognitive Training alone (CT), combined Physical And Cognitive Training (PACT) and Waitlist Group (WG). The PT group will perform exercises (flexibility, endurance, strengthening, and balance training) for 60–90 min three times per week for 12 weeks. The CT group will be involved in a paper-based training focusing on orientation, memory, attention and executive functioning for 60–90 min per session, once a week for 12 weeks. The PACT group will undergo cognitive training incorporated in physical exercise for 60–90 min three times per week for 12 weeks. The WG will receive the intervention, combined physical and cognitive training, at a later date. Assessors blinded to participant allocation will conduct pre-intervention, post-intervention, and 6-month follow-up assessments. The primary outcome measure will be falls rate. The secondary outcome measures will be Physiologic Profile Assessment and Falls Risk for Older Persons in the Community, and assessments that evaluate cognitive, physical and psychological factors related to falls.

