### Sample size computation

The sample size and power calculations will be based on fall rate which is the primary outcome of the study. Using statistical software Gpower 3.1.9.2, a priori power analysis was conducted using the computed effect size (Cohen’s d = .39) from Trombetti et al. (2011) [46]. Assuming 80% power with 5% Type 1 error and four groups, the calculated total sample size is 80. Considering a 16% dropout rate (Trombetti et al., 2011) [46], the total number of participants is inflated to 93. There should be at least 23 participants per group.

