### Primary outcome measure

#### Falls rate

Each participant will be given a calendar diary to mark any incidence of fall on a weekly basis during the assessment period. A relative or caretaker of the older person will be asked to validate the information. The confirmation by another person is done because self-reporting techniques, particularly for individuals with cognitive impairment, may not be accurate due to recall bias [53]. Monthly phone calls will be done to update the falls history of each participant.

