### Statistical analysis

Descriptive statistics will be used to summarize demographic data using mean standard deviations, and percentages. Baseline values across the groups will be compared using one-way ANOVA for interval/ratio data and Kruskal-Wallis test for nominal/ordinal data. The multivariate repeated measure ANOVA will be used to determine the pre- and post-intervention effects and differences among group data with a normal distribution; otherwise the Friedman test will be utilized. The incidence rate ratio, computed as the number of falls divided by the duration of falls monitoring for every participant, will be used to compare intergroup fall rate. An intention-to-treat analysis will be used for missing data due to dropouts. The *p*-value of < 0.05 is considered significant. Data analysis will be performed using SPSS version 23 for Windows.

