## Appendix

**Table 4 Tab4:** Timeline of the study

Research Highlights	Actual/Expected dates of implementation
Participant recruitment	June–September 2017
Baseline assessment	August–September 2017
Randomization	September 2017
Post-treatment assessment	December 2017–January 2018
9mons post baseline assessment	June–July 2018
Study completion	August 2018

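### The primary-outcome formula is labelled an incidence rate ratio but defines an individual fall rate: it contains no between-arm ratio and does not say how unequal monitoring time enters

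*Protocol article*

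**What the plan says.** The Abstract (Methods/design) names a single primary outcome: "The primary outcome measure will be falls rate". Sample size computation ties the trial's size to it: "The sample size and power calculations will be based on fall rate which is the primary outcome of the study". Under Falls rate, the data source is a weekly diary: "Each participant will be given a calendar diary to mark any incidence of fall on a weekly basis during the assessment period". Someone close to the participant confirms the entries, and monthly calls update them.

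Statistical analysis has one sentence addressed to falls. It begins "The incidence rate ratio, computed as the number of falls divided by the duration of falls monitoring for every participant, will be used", and its purpose follows: "will be used to compare intergroup fall rate".

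Two further statements bear on monitoring time. The sample size section anticipates losses ("Considering a 16% dropout rate"), and Statistical analysis says of them only "An intention-to-treat analysis will be used for missing data due to dropouts". The Appendix timeline has a "9mons post baseline assessment", which agrees with 12 weeks of training plus six months of follow-up.

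**The concern.** The name and the formula describe different quantities. Carried out as written, the formula yields one rate per participant and no effect of one arm relative to another. The hypothesis in the Background is that PACT prevents falls better than PT or CT alone, so the effect that should answer it is not defined.

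This is not detail that a condensed article leaves to an analysis plan. The article states a formula, and a later plan would have to contradict it to report a rate ratio.

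The wording can be completed in more than one way, and the choice affects precision and error rates. Averaging or testing the individual rates gives a participant watched briefly the same weight as one watched throughout. Pooling falls and person-time by arm and attaching a Poisson interval ignores the fact that some people fall repeatedly. If the choice is not fixed in advance, it can be made after the data are seen.

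**Working it through.** **1. Definition.** Let participant *i* have *y_i* falls in monitoring time *T_i*.
- The formula as written is *y_i / T_i*, the individual's incidence rate, in falls per unit time.
- The rate in arm A is Σ*y_i* / Σ*T_i* over that arm.
- The incidence rate ratio of A to B is (rate in A) / (rate in B), which has no unit.

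The written formula has no second arm and carries a unit of time, so it cannot be the third quantity.

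**2. Inputs for size.** From the article: at least 23 per arm, 16% dropout, and about nine months of monitoring (39 weeks, 0.75 year). The article gives no fall rate, no dispersion and no timing of dropout, so there is no figure of its own to reproduce on this point. Assumed here: true rate λ = 1 fall per person-year; dispersion φ (between-person variance of the rate relative to λ²) of 0 or 1; the 16% leave at times spread evenly between one week (0.0192 year) and 0.75 year, for reasons unrelated to falls.

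**3. What equal weighting does in one arm (illustration).** Twenty-two people are each watched for 0.75 year and have 11 falls in all; one person is watched for one week and falls once.
- Unweighted mean of individual rates: the 22 average (11/22)/0.75 = 0.667 per year and the last has 1/0.0192 = 52.2 per year, so (22 × 0.667 + 52.2)/23 = 2.91 per year.
- Total falls over total time: 12/(22 × 0.75 + 0.0192) = 0.73 per year.
- If the last person is watched for 12 weeks instead, the figures are 0.83 and 0.72.

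This shows the mechanism in one unlucky arm; it is not the expected result.

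**4. Average cost of equal weighting.** Both estimators centre on λ when exit is unrelated to falls. Their variances are
- unweighted mean: (1/n)[λ E(1/T) + φλ²]
- pooled rate (approximately): (1/n)[λ/E(T) + φλ² E(T²)/E(T)²]

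With the inputs above:
- E(T) = 0.84 × 0.75 + 0.16 × 0.385 = 0.692, so 1/E(T) = 1.446
- E(1/T) = 0.84/0.75 + 0.16 × ln(0.75/0.0192)/(0.75 − 0.0192) = 1.923
- E(T²) = 0.503, so E(T²)/E(T)² = 1.052

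Variance ratio, unweighted to pooled:
- φ = 0: 1.923/1.446 = 1.33
- φ = 1: (1.923 + 1)/(1.446 + 1.052) = 1.17

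Simulation of 40,000 arms of 23 agrees: both means were about 1.00, and the variance ratios were 1.34 and 1.18.

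**5. Cost of the other completion, pooled Poisson.** With SE(log ratio) = √(1/d₁ + 1/d₂), where d₁ and d₂ are the falls in each arm, the true variance is larger by a factor of about 1 + λTφ. For λ = 1, T = 0.75 and φ = 1 the factor is 1.75. A nominal 5% test then rejects about as often as |Z| > 1.96/√1.75 = 1.48, or about 14%. Simulated two-sided type I error (100,000 replicates, 23 per arm, 39 weeks, no dropout, equal true rates):

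| Rate per year | φ | Type I error |
|---|---|---|
| 1.0 | 0.5 | 8.6% |
| 0.7 | 1 | 10.1% |
| 1.0 | 1 | 12.9% |
| 1.5 | 1 | 17.0% |
| 1.0 | 2 | 20.1% |

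**The case against.** The sentence does not stop at the formula: it says the measure serves an intergroup comparison. A charitable reader will say the authors named the ratio as the contrast and then described the rate that goes into it. That stands as to intent. A reader might infer that the protocol compares no arms at all, and the text does not support this. The formula is still wrong for the quantity it names.

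A reader might also take it as settled that a participant watched for a week counts as much as one watched for nine months. No step of averaging or testing unweighted rates is stated. Each person's falls and monitoring time are also the inputs to a count model with an offset. Equal weighting follows from the literal reading, but it is an inference. A Poisson interval is likewise named nowhere, so the inflated type I error belongs to a possible completion of the plan and not to the plan itself.

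The most tempting extension is that falls cause withdrawal, which would bias individual rates upward because the fall shortens its own denominator. The documents give no basis for this:
- Participants lists false information, raised blood pressure, and fever or body pains as grounds for ending participation.
- The Discussion expects dropout from busy schedules, relocation, low motivation and disease.
- Adverse events answers a fall with first aid, medical attention or referral, not withdrawal.
- Falls are tracked by diary and telephone, so leaving the sessions need not end falls monitoring.

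The size of any such bias would also depend heavily on the shortest monitoring time assumed. No bias of this kind is claimed here.

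Finally, when dropout is unrelated to falls the loss is moderate, and negative binomial regression is not the only sound choice. Both points stand.

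**Conclusion.** The definition is wrong as written and should be corrected before the falls data are analysed. What is labelled an incidence rate ratio is a per-participant incidence rate, the between-arm ratio is not expressed, and the use of unequal monitoring time is not stated. This part rests on the text alone and needs no assumption.

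The size of the consequence depends on how the sentence is completed. Unweighted individual rates cost about 17–33% in variance with no bias; this assumes 1 fall per person-year, dispersion of 1 or 0 respectively, 23 per arm, nine months, and 16% leaving at evenly spread times unrelated to falls. A pooled Poisson interval would have a type I error of about 9–20% instead of 5%, for assumed rates of 0.7–1.5 per year and dispersion 0.5–2. Neither method is stated in the article, and neither figure is a prediction for this trial.

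**What to change.** Replace the falls sentence in Statistical analysis with wording that does three things:

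1. Call falls divided by person-time the fall rate, and report it per arm as total falls over total person-years.
2. Define the incidence rate ratio as one arm's fall rate divided by another's.
3. Estimate it from falls per participant by a count model that allows for over-dispersion (for example negative binomial regression, or Poisson regression with robust standard errors), with log(monitoring time) as offset and arm as factor. Report it with a 95% CI for PACT versus PT, PACT versus CT and PACT versus WG.

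The cost is one or two sentences. The model uses only the fall counts and monitoring times already planned. Its intervals will be wider than naive Poisson ones, and a negative binomial fit may have trouble converging if falls are few, so a fallback such as the robust Poisson model should be named in advance.

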Older adults will be excluded if they have a diagnosis of dementia or Alzheimer’s disease; had history of major medical conditions such as cerebrovascular disease, cardiopulmonary condition, serious musculoskeletal disease, cancer, major psychiatric condition; have severe visual and/or hearing impairment; or are illiterate that will hinder them in participating fully and safely in the exercise and/or cognitive training programs. Furthermore, those who have been taking medications such as sedatives, antidepressants, diuretics, anti-epilepsy that might affect their cognitive function will not be included. Deliberately providing false information is a reason for termination of participation. Elevation of blood pressure beyond the expected increase due to exercise or the presence of fever and body pains for several days due to other causes may be reasons for withdrawal to participate. To enhance adherence to the intervention, participants will be receiving a travel allowance and light refreshments every time they attend sessions.

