### Outcomes measures

The following primary and secondary outcome measures will be performed by trained assessors blinded to the group allocation. Measurements will be taken at baseline, at the conclusion of the intervention period, and 6 months post-intervention. Additional information regarding the exercise behavior and the physical and social activities participated in by the eligible participants in the last 6 months will be obtained during the 6 months post-intervention follow-up assessments [52].

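### For the repeated secondary outcomes, intention-to-treat is named as the missing-data method, but the tests it is paired with exclude anyone who misses an analysed visit

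*Protocol article*

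**What the plan says.** All the analysis statements are in the protocol article, Statistical analysis.

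- **Repeated outcomes, normally distributed:** "The multivariate repeated measure ANOVA will be used to determine the pre- and post-intervention effects and differences among group data with a normal distribution".
- **Repeated outcomes, otherwise:** "otherwise the Friedman test will be utilized".
- **Missing data:** "An intention-to-treat analysis will be used for missing data due to dropouts". No imputation, last-value or likelihood-based method is named.
- **Falls rate (primary outcome), handled separately:** "computed as the number of falls divided by the duration of falls monitoring for every participant, will be used to compare intergroup fall rate".
- **Software:** "Data analysis will be performed using SPSS version 23 for Windows".

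The Outcomes measures section gives the visits: "Measurements will be taken at baseline, at the conclusion of the intervention period, and 6 months post-intervention". Sample size computation allows for 16% dropout and raises the total from 80 to 93. The Discussion expects people to leave for reasons that include low motivation and illness. The Participants section says that an exercise-related blood-pressure rise larger than expected, or several days of fever and body pain from other causes, "may be reasons for withdrawal to participate".

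**The concern.** Intention-to-treat and missing-data handling answer different questions. The first fixes the analysis set and the arm to which each person belongs. The second says what is done when a member of that set has no measurement. The article names the first as though it were the second.

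The named tests make this more than loose wording. Multivariate repeated-measures ANOVA treats each participant's visits as one vector, and Friedman ranks visits within complete blocks. Both exclude a participant with a gap in the visits analysed. The sentence promises that everyone randomised is kept, while the tests as specified keep only those with complete data.

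Falls rate is primary, but the secondary outcomes matter: reduced risk of falls is the second half of the trial's hypothesis, and it rests on them (PPA, FROP-Com, and the cognitive, physical and psychological measures). If those who leave are less healthy or less motivated than those who stay, a completer analysis no longer compares the groups that were randomised.

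**Working it through.** **Inputs.** From Sample size computation: 80 before dropout, 16% dropout, 93 after, four groups, 5% type 1 error, 80% power, effect size 0.39. From Outcomes measures: three visits, two of them after baseline.

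**1. The plan's own figure.** 80 × 1.16 = 92.8, rounded up to 93. The stated total reproduces. (Dividing instead, 80 / 0.84 = 95.2, gives 96; that is a separate matter.)

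**2. Loss at the planned dropout.** This assumes that each dropout misses at least one analysed visit.

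- Excluded: 93 × 0.16 = 14.9, about 15.
- Complete: 93 × 0.84 = 78.1, about 78, slightly below the 80 the plan set out to analyse.

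**3. Range.** The documents do not give the share missing at each visit, nor say whether all three visits enter one model. Let m be the share missing at each post-baseline visit, independently (an assumption). Complete cases are 93 × (1 − m) if only baseline and one later visit are modelled, and 93 × (1 − m)² if all three are.

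| m | Baseline plus one later visit | All three visits |
|---|---|---|
| 5% | 88 | 84 |
| 10% | 84 | 75 |
| 16% | 78 | 66 |
| 20% | 74 | 60 |

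**4. Power, as a rough scale only.** One-way ANOVA, four groups, 5% level, noncentral F with noncentrality N × f² and f = 0.39. Two cautions apply: the article labels 0.39 as Cohen's d, and the calculation was made for falls rate, not for the secondary outcomes. Power is about 88% at N = 93 and 81% at N = 78. In the three-visit column it is about 85%, 80%, 73% and 68% from top to bottom. At the planned dropout, power is not the main loss.

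**5. Is bias certain?** No. In an illustrative simulation of two arms and three visits (all correlations 0.5, true effect 0.5 SD at both later visits), about 16% of each arm lost the last visit. Loss was random in the control arm and related to a low post-intervention value in the active arm. The completers' difference in change from baseline was 0.497 against a true 0.5. With equal correlations, selection on the middle visit shifts the first and last visits equally, so it cancels in the change. Bias therefore depends on the dropout mechanism and the correlation pattern, neither of which is known here.

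**6. Could loss differ by arm?** PT and PACT have 3 × 12 = 36 sessions, CT has 12, and the waitlist group has none while waiting. A withdrawal reason tied to exercise-related blood pressure has more opportunity to apply in the exercise arms. That makes unequal loss plausible; the documents give only one overall rate.

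**The case against.** The best defence is that the sentence shows an intention to keep dropouts in the analysis, with values filled in by a method described elsewhere. Imputation detail is commonly left to an analysis plan or full protocol, and neither is shown. The article nowhere says that incomplete participants are deleted. This has force: completers-only is what follows from the tests as written, not something the article states. But the article does not leave the matter open. It names a remedy for missing data that is not one, and pairs it with tests that require complete data.

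Several stronger readings are tempting, and the documents do not support them:

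- **That the whole trial analysis is completers-only.** Falls rate divides by each participant's own monitoring duration, so a dropout with some diary or telephone follow-up can still contribute.
- **That a missed 6-month visit necessarily removes someone from the post-intervention comparison.** This holds only if all three visits enter one model. The text speaks of pre- and post-intervention effects and does not say so.
- **That the withdrawal reasons can arise almost only in the active arms.** Fever and body pain from other causes can occur in any arm. The Adverse events section describes vital-sign checks at sessions but does not say they are taken nowhere else. Waitlist members also have diaries and telephone contact. Only the blood-pressure reason is tied to exercise.
- **That dropout does differ by arm, in a known direction.** No arm-specific figure is given.

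A mixed model is also not the only sound remedy; named multiple imputation before the planned tests would resolve the inconsistency too.

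**Conclusion.** The point holds for the repeated secondary outcomes and not for the primary falls rate. Intention-to-treat is misnamed as a missing-data method, and the tests specified beside it would in practice give completer analyses that conflict with it.

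The size is about 15 of 93 randomised participants excluded and about 78 left, if the planned 16% dropout occurs, each dropout misses an analysed visit, and nothing is filled in beforehand. Missed visits among people who stay in the trial would add to this. The loss of power is modest at the planned rate. Bias is possible, because the article itself expects people to leave through illness and low motivation, but its direction and size are not established. Unequal loss between arms is an assumption that the blood-pressure withdrawal reason makes plausible.

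**What to change.** 1. **Analysis set.** State it separately from missing-data handling: all randomised participants, in their allocated arm.
2. **Continuous secondary outcomes.** Replace repeated-measures ANOVA with a linear mixed model for repeated measures, with arm, visit, arm-by-visit interaction and baseline value, unstructured covariance, and all available visits. The named software can fit it. With baseline as a covariate, a participant with no post-baseline visit still adds nothing to the estimate, so report that number by arm.
3. **Outcomes otherwise sent to Friedman.** Use a model that also keeps incomplete participants, such as an ordinal or generalised mixed model, or multiple imputation with its method named.
4. **Sensitivity.** The mixed model assumes that missingness depends only on observed data. Add a sensitivity analysis that departs from this.
5. **Follow-up.** State that stopping the programme does not by itself end diary, telephone and assessment follow-up unless consent is withdrawn. This leaves the withdrawal reasons themselves untouched.

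The falls analysis needs no change on this account. The cost is revised wording, slightly more analysis work, and a few more contacts with people who stop attending.

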### Data monitoring

Collected data using a paper-based assessment kit will be encoded in MS Excel by one study personnel blinded to the group allocations. This will be double-checked by another research assistant. The privacy and confidentiality of the participants will be kept by making no personal information available to the public. Signed consent forms and filled data collection sheets will be stored in a locked cabinet. The encoded data will be kept in a password-protected computer folder. Data will be stored for five years and will then be deleted. In the event of any publication involving this study, the participants’ identities will remain confidential. Aside from the researchers, the study monitors from the ethics committee will be granted monthly direct access to the records for purposes of procedure and data verification and interim analyses. Any modifications in the study procedure will be reported to the Human Subjects Ethics Sub-committee of The Hong Kong Polytechnic University-Department of Rehabilitation Sciences and the Ethics Review Committee of the University of Santo Tomas-College of Rehabilitation Sciences, and to ClinicalTrials.gov. To disseminate the findings of this research, the results and implications will be reported to the participants and presented formally in professional conferences, and published in a reputable journal.

